**Visual Analog Scale (VAS)**

The VAS is a one-dimensional scale used to measure pain intensity consisting of a 10-cm horizontal line with zero at one end (accompanied by the expression "no pain") and 10 at the other end ("unbearable pain"). Pain will be classified as mild (1 to 3 cm), moderate (4 to 6 cm) or strong (7 to 9 cm). The absence of pain (score: 0) indicates that the volunteer has no difficulties performing activities of daily living; mild pain indicates the ability to perform activities despite pain; moderate pain partially or completely hinders activities and performance is compromised; and strong pain completely impedes the execution of activities^36^.

**Randomization**

Prior to the intervention, the volunteers will be randomly allocated to two different groups. Randomization will be performed by an independent researcher using a simple lottery system with sealed opaque envelopes immediately after the baseline assessment. The volunteers will be considered participants in the study the moment the envelope is opened. The participants will be randomized to receive the following distinct interventions:

Group I: Twenty volunteers will undergo VR with virtual reality (balance games) using the Wii® console, Wii-Remote and Wii Balance Board (Nintendo).

Group II: Twenty volunteers will undergo VR with virtual reality (balance games and muscle strength games) using the Wii® console, Wii-Remote and Wii Balance Board (Nintendo).

The games will last from 30 minutes to one hour, with sessions twice a week for 10 weeks (total: 20 sessions).

**Treatment**

All participants will receive orientation regarding the rehabilitation procedure. The VR will involve virtual reality with the use of the Wii Fit Plus®, Wii-Remote and Wii Balance Board (Nintendo). The Wii Balance Board (WBB) is a platform with sensors that detect the position and orientation of the gamer. In some games, the player must perform the same movement he/she would do in a real game. The VR with virtual reality games will be performed in both groups for 30 minutes twice a week for a total of 20 sessions. Group I will play five balance games. Group II will play the same five balance games plus four strength games. The games will be selected to favor changes in balance and postural instability. After completing the collection of all data, to ensure the same rehabilitation for both groups, will be available the training with strength exercises to group I.

The following are the balance games performed on the WBB:

Soccer Heading®

Table Tilt®

Tightrope Walk®

Penguin Slide®

Perfect 10®

The muscle strengthening exercises were selected to improve balance, which depends on the interaction between vision, vestibular and peripheral sensations, central commands and neuromuscular responses:

Single leg extension®

Torso Twist®

Sideways Leg Lift®

Single Leg Twist®

The training phases will be performed simultaneously, avoiding complications and alterations that may compromise the validity of training. The assessment will be performed again after the 20 intervention sessions.

The time schedule of enrolment, interventions, assessments and visits for participants are describe in Table 2 in accordance of Spirit checklist (Figure 1)

**Management**

The researches ensure that the anonymous character and the confidentialityof participants, dealing with people or data files, will be maintained and their identities or any kind of identification will be protected. The clinics records, research instruments or any document that can be used, containing data of participants, will not be identified by the name, but through a code, even when submitted to regulatory institutions or sponsors. Researchers willmaintain the record of inclusion of participants confidentially, containing codes, names and addresses for their own use. The files of the Consent forms will be issued in two copies each one of them to be known and signed by participants, researchers and researched (or legal representatives), the files will be maintained by the researcher in strict confidence, all together, in a single file related to that research. We ensure that participants that comprise the casuistry will receive an original copy of the Consent term.

There is no personal expense for the participant in any stage of the study, instead, all assessment shall be free, including the otorhinolaryngological evaluation, PPA and dynamometer. There is also no financial compensation related to your participation. If there is any additional expense, it will be absorbed by the research budget. Participation in this study is completelyvoluntary and non-participation does not imply any change in your medical follow-up, not even will change the relationship between the team and the patient. After signing the Consent term, you will have total liberty to take it out at any moment and leave participatingin the study, if desired, without any damage to the development of the treatment and follow-up at the institution.

The results of this research may be presented in at meetings or publications, however, your identity will not be revealed in these presentations.

The risks during the research are minimal or non-existent, but the realization of the assessment and rehabilitations may cause discomfort, arising from the direct interference on the vestibular system responsible for the balance. The support in this sense may be momentary interruption of the evaluation VR, until medical interventions if necessary. However, if persists the discomforts the participant will be removed from the research and the data collected will be excluded from the sampling, and the patient will not be reallocated in any group.

As a strategy to improve the adhesion to intervention protocols, will be promoted phones contacts for confirmations of treatments sessions, as well as will be available through reports the results of assessment which the participants are submitted.

The only intervention not permitted will be related to the conventional vestibular rehabilitation and virtual.

This work was supported by the authors by themselves.

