**Control of bias**

The study includes several important methodological resources that will minimize the risk of bias, such as the randomization process, allocation concealment, blinded assessment of the results and intention-to-treat analysis.

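### Participants removed for persistent discomfort after randomisation leave the analysed sample and no outcome counts them, so a tolerability difference between the groups can be masked

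*Protocol*

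**What the plan says.** The protocol's Management section describes the risk in one sentence that qualifies itself: "The risks during the research are minimal or non-existent, but the realization of the assessment and rehabilitations may cause discomfort". It gives the source of the discomfort as "arising from the direct interference on the vestibular system responsible for the balance". The foreseen response is graded: "The support in this sense may be momentary interruption of the evaluation VR, until medical interventions if necessary". The last step is a removal and data rule: "if persists the discomforts the participant will be removed from the research and the data collected will be excluded from the sampling". The same sentence adds that the patient is not placed in another group. The rule is identical for both groups.

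Three other sections bear on this:

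- Randomization places the envelope draw immediately after the baseline assessment and states: "The volunteers will be considered participants in the study the moment the envelope is opened".
- Control of bias lists, among the safeguards, "blinded assessment of the results and intention-to-treat analysis".
- Assessment of results names ten tools as primary outcomes and four secondary outcomes built from the same tools. None is an adverse event, an episode of discomfort, an interruption or a removal.

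The groups differ in one respect, stated under Treatment: "Group II will play the same five balance games plus four strength games".

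**The concern.** Persistent discomfort severe enough to end participation is itself a result of the trial. It shows how well the assigned programme was tolerated. Under the Management rule, a participant who has this result after allocation leaves the analysed sample because of it, and the list of outcomes has no place where the event would be counted.

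Two things are at stake. First, the comparison is no longer between the groups as randomised but between those in each group who tolerated their programme, which an intention-to-treat analysis is meant to avoid. Second, the trial asks whether the longer set of games is better than the shorter one. A reader deciding that needs to know how many in each group could not continue. If the numbers differ, the plan as written has no outcome in which the difference would show.

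Restoring the efficacy scores of removed participants would repair the first problem but not the second. A score on a balance scale does not record that someone stopped because of dizziness.

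**Working it through.** The protocol gives no figure for discomfort, dropout or removal, so there is nothing to reproduce. The check is mainly a reading of the sections together, followed by an illustration on assumed rates.

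**Reading**

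1. *Timing.* Discomfort may come from assessment or rehabilitation. Discomfort at the baseline assessment precedes the envelope, and excluding such a person does not affect the randomised comparison. Discomfort during the 20 sessions or at the second assessment follows the envelope, so a removal then is post-randomisation.
2. *Analysis set.* Management takes these participants' data out of the sample. Control of bias promises analysis by intention to treat. Both cannot be followed for the same participant.
3. *Can a listed outcome recover the event?* Pain (VAS) and the functional tools are applied before rehabilitation and after session 20. An event in between need leave no trace in them, and a removed participant's scores are excluded. The secondary outcome named for fewer falls uses FES-I, the ABC scale, the VADL scale and the dynamometer. As the protocol describes them, these measure fear, confidence, dependence and strength; none counts falls.

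**Illustration**

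Inputs: 20 participants per group (Randomization). The rates p of persistent discomfort leading to removal are assumptions.

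Expected removals = 20p. Chance of at least one removal = 1 − (1 − p)^20.

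| Assumed p | Expected removals | Chance of at least one |
|---|---|---|
| 5% | 20 × 0.05 = 1 | 1 − 0.95^20 = 64% |
| 10% | 20 × 0.10 = 2 | 1 − 0.90^20 = 88% |
| 20% | 20 × 0.20 = 4 | 1 − 0.80^20 = 99% |

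Suppose two of 20 in one group are removed and excluded, and their removal is not reported separately. The analysed sample then shows 0 of 18 (0%), where the randomised group had 2 of 20 (10%).

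**Precision available at this size**

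With no events, the exact two-sided 95% upper limit is 1 − 0.025^(1/n):

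- n = 20: 1 − 0.025^(1/20) = 16.8%
- n = 40: 1 − 0.025^(1/40) = 8.8%

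These limits follow from sample size alone and would be the same under perfect recording. They are not evidence of the defect. They show how much an observed zero could support, and why counts should carry intervals.

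**The case against.** The strongest reply is that a by-group harms table is commonly left to a statistical analysis plan, which may exist, and that a missing harms outcome is an omission rather than an error. That would stand if the protocol were merely silent. It is not: it states a rule that takes the affected participants out of the sample, and it also promises intention to treat. An analysis plan cannot follow both, nor recover events that were never recorded.

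Other parts of the reply do stand, and they rule out several stronger readings:

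- *That harms cannot appear at all.* Only persistent discomfort triggers exclusion. Participants with transient discomfort stay in, and worsening in pain, fear of falling, balance or fall risk can show among those who complete. Nothing forbids reporting removals with their reasons.
- *That the data are destroyed.* The wording concerns exclusion from the sample, not deletion.
- *That the rule hides harm from the strength games in particular.* Management attributes discomfort to vestibular interference from procedures that both groups undergo. It does not mention the strength games, and the Exclusion criteria remove users of gait aids and people with significant musculoskeletal conditions. A special risk in Group II is an inference, and the point does not need it: one rule applied to both groups still masks any difference in removals, in either direction.
- *That the risk statement flatly contradicts itself.* The sentence concedes discomfort at once, and discomfort eased by a short pause fits a minimal risk. Only the suggestion of no risk sits badly with possible medical intervention. That is loose wording and causes no loss of data.

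**Conclusion.** The point holds as a conflict between sections with a consequence for tolerability. Management excludes participants after randomisation because of their reaction to trial procedures, Control of bias promises intention to treat, and no listed outcome counts the events. Followed as written, the plan can mask a difference in tolerability between the groups.

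The size cannot be fixed from the protocol. On the assumed rates of 5% to 20%, between 1 and 4 removals per group of 20 would be expected. If nobody is removed for persistent discomfort after allocation, the exclusion has no effect, though lesser events would still go uncounted. The illustration also assumes that removals are not reported by another route; the protocol neither requires nor prohibits that. The direction of any bias is unknown. The documents do not show that either group is more exposed.

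**What to change.** - Reconcile Management with Control of bias so that the exclusion does not apply to tolerability reporting.
- Report by group the number of participants with discomfort leading to interruption, with a medical intervention, with a fall during a session, and with removal (with reasons). Use all randomised participants as the denominator, including those removed, and give exact 95% intervals.
- Record these events prospectively in the remaining sessions. The Timeline says that recruitment is complete and treatment is due to end by July 2021, so use whatever records exist for past sessions and state the gaps. The protocol does not say that session notes were kept.
- Make the risk wording in Management consistent with the events that the same section foresees. This is an editorial change.

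No change to the clinical rule on interruption or removal is proposed.

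The cost is a brief entry per session and one table, with no extra staff, visit or procedure. The downside is that the safety statement may become less favourable and that the past data may be incomplete.

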**Physiological Profile Assessment**

The physiological profile assessment (PPA) is a validated assessment tool for the risk of falls developed by Lord, Menz and Tiedemann *et al*.^12^. Performs direct assessment of sensory motor skills. The score indicates the degree of risk: <0 = low risk, 0-1 = mild risk; 1-2 = moderate risk; and> 2 = high risk of falls, indicating the individual's performance in comparison to the normative values for each age group.

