**Berg Balance Scale (BBS)**

The Brazilian version of the BBS, which was cross-culturally adapted to the Brazilian population by Myamoto *et al.*^18^, will be used to determine risk factors for the loss of independence and falls. The maximum score is 56 points, with higher score denoting better balance. The score is analyzed to determine the degree of the risk of falls: low, medium, high or 100% risk.

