**Timed Up and Go (TUG) test**

According to Paula, Alves Jr. and Prata^32^, the TUG test consists of standing up from a chair without using the arms, walking three meters, turning around, walking back to the chair and sitting down again. The test begins and ends with the volunteer seated with the back against the backrest of the chair. The volunteer begins with the command "go" and the time needed to complete the task is timed with a stopwatch. According to the literature, there is no consensus on the results of this test. However, Guimarães *et al*.^33^ established the following markers: less than 10 seconds to complete the TUG test indicates a low risk of falls; 10 to 20 seconds indicates a medium risk and more than 20 seconds indicates a high risk of falls.

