**Possible effects of treatment**

The main clinical manifestation of HSP is a pyramidal pattern of slowly progressive weakness^5^associated with lower limb weakness and progressing to other manifestations, such as dementia, peripheral neuropathy, Parkinson's disease and ataxia.

The aim of VR with virtual reality is to delay the progression of the disease, providing a differentiated, accessible, low-cost treatment option. The use of virtual reality with Nintendo Wii® is a novel, playful, multisensory tool for balance training that engages the patient with enthusiasm and motivation during the continuous sessions. This technological resource is an additional tool to other conventional methods of VR.

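### The protocol's risk statement allows that risks may be absent, does not name falls, and provides no response to or record of a fall during balance-board training

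*Protocol*

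**What the plan says.** The protocol's statement on participant risk is in Management: "The risks during the research are minimal or non-existent, but the realization of the assessment and rehabilitations may cause discomfort". It attributes the discomfort to interference with the vestibular system and continues: "The support in this sense may be momentary interruption of the evaluation VR, until medical interventions if necessary". If the discomfort persists, the participant is removed and the data are excluded. No section names a fall as a risk of the assessments or the training.

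Other sections bear on this:

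- **Disease.** Possible effects of treatment describes a slowly progressive weakness, "associated with lower limb weakness and progressing to other manifestations", with ataxia among the examples.
- **Exposure.** Under Randomization and Treatment, both groups have 20 sessions with five games on the Wii Balance Board. In addition, "Group II will play the same five balance games plus four strength games".
- **Fall-risk grading.** For the Berg scale: "The score is analyzed to determine the degree of the risk of falls: low, medium, high or 100% risk". The PPA bands end with "and> 2 = high risk of falls". For the TUG, "more than 20 seconds indicates a high risk of falls".
- **Safeguards.** Exclusion criteria removes users of gait aids, people who cannot follow simple commands, and people with significant musculoskeletal conditions, severe visual impairment or other impeding abnormalities. Quality assurance has two skilled researchers deliver the sessions, both with experience of this protocol in spinocerebellar ataxia and Parkinson's disease.
- **Outcome.** In Assessment of results, secondary outcome 3 is a reduction in falls, evaluated by FES-I, ABC, VADL and the dynamometer.

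**The concern.** A fall is the foreseeable injury when people with weak legs train on a balance board. The risk statement allows that there may be no risk at all, and the rest of the protocol does not support that.

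Two consequences follow if the text is applied as written. A session is paused and medical help given for discomfort, but nothing is stated for a fall. And a fall in training would not show in the results, although fewer falls is a declared aim and one group does additional strength games, two of which are single-leg exercises by name. A difference between the groups in training falls could go unseen.

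**Working it through.** The protocol gives no fall rate and no count of participants at high fall risk, so there is no figure to reproduce and no expected number of falls to derive. The check sets the sections side by side.

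1. **Who is exposed, and how often.** Study population gives 40 participants, and Randomization gives 20 per group and 20 sessions each.
   - Planned sessions: 40 × 20 = 800, or 20 × 20 = 400 per group.
   - Games: five in Group I and 5 + 4 = 9 in Group II. The five shared games are played on the board, so every participant is exposed.

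2. **Does eligibility remove those likely to fall?** Only in part. The criteria exclude gait-aid users and several impairments, but set no limit on the Berg, PPA or TUG result. Someone who walks unaided and scores in a high-risk band remains eligible.

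3. **Does the stated response cover a fall?** Management introduces the interruption and medical intervention as support for the discomfort it has just described. The removal rule that follows also depends on persisting discomfort. A fall is a different event, and neither sentence reaches it.

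4. **Would a training fall be recorded?** The instruments for secondary outcome 3 are described as follows:

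| Instrument | What the protocol says it measures |
|---|---|
| FES-I | Fear of falling |
| ABC | Confidence in balance during daily activities |
| VADL | Effect of dizziness and imbalance on dependence |
| Dynamometer | Muscle strength |

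   None is described as counting falls. The FES-I section says most items distinguish people who have fallen from those who have not, but that is a validity property and not a count. The instruments are applied at baseline and after session 20. No section provides for noting a fall between those visits.

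5. **Could an analysis plan supply this?** An analysis plan can say how recorded falls are summarised. It does not set the risk statement, the response during a session or what is collected there. Those belong in the protocol.

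**The case against.** The strongest reply is that the sentence offers minimal as an alternative to non-existent, and nothing shows minimal to be wrong. The high-risk bands belong to the scales in general and do not show that any enrolled participant falls in them. The TUG section itself notes a lack of consensus on that test. Participants walk without aids, an otolaryngologic screen and a general exclusion for impeding abnormalities apply, and experienced researchers run the sessions. All of this stands. It answers a claim that the risk is large, which is not made here. It does not support a statement that risk may be absent, and it supplies neither a response to a fall nor a record of one.

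Some stronger readings are tempting but not supported:

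- A reader might infer that participants train unsupervised. Quality assurance says two skilled researchers perform the treatment. How closely they stand by is operational detail that a session manual can hold.
- A reader might infer that participants were misinformed at consent. The consent pages are not available for review, so nothing can be said either way.
- A reader might want to attach a confidence limit for zero observed falls. Such a limit follows from the number of participants alone and says nothing about this training.
- A reader might take the conclusion's reference to cost-benefit as a promise to compare harms between groups. That passage presents a low-cost treatment option and makes no such promise.

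**Conclusion.** The point holds as a small correction to the safety text. The protocol states a level of risk that its own description of the disease, the training and the eligibility criteria does not support, and it leaves a training fall without a stated response or record. The exposure is 40 participants over 800 planned sessions. The number of falls to expect is unknown, and none is assumed.

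The conclusion rests on two readings: that the support sentence in Management refers to the discomfort named just before it, and that the four instruments measure only what their sections describe. No estimate, error rate or sample size changes. The gain is in safety and in being able to report falls by group.

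**What to change.** In Management:

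1. Delete the wording that the risks may be non-existent.
2. Name falls during assessment and training as a risk, alongside discomfort.
3. Apply the existing interruption and medical intervention to a fall as well as to discomfort. Do not carry over the rule that removes the participant and excludes the data: applied to fallers, it would conflict with the intention-to-treat analysis promised under Control of bias.
4. Have the treating researchers log each fall by participant code, session and game, and report the falls by group.
5. Keep the log from the blinded examiner until the final assessment is done. An entry for a strength game would reveal the group, since only Group II plays those games.

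Eligibility, the therapists' masking to baseline results, the outcomes and the ANOVA stay as they are, and no extra staff are needed.

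The cost is a small recording task, a notice to the ethics committee and possibly informing participants already enrolled. Timeline says recruitment is complete and treatment was due to end by July 2021, so the new response and log can apply only to sessions still to be delivered.

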**Study population**

Forty patients with a diagnosis of HSP will be recruited from the hospital of the Federal University of Parana in the city of Curitiba, Brazil. To participate, the volunteers must meet the following eligibility criteria:

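### Excluding the data of participants with persisting discomfort contradicts the promised intention-to-treat analysis and can bias the comparison if discomfort tracks outcome and differs by arm

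*Protocol*

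**What the plan says.** Four places in the protocol bear on this.

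- **Management** names the source of the risk: "the realization of the assessment and rehabilitations may cause discomfort, arising from the direct interference on the vestibular system". If the discomfort persists, "the participant will be removed from the research and the data collected will be excluded from the sampling". The same sentence ends by ruling out a transfer between arms: "the patient will not be reallocated in any group".
- **Randomization** places the draw immediately after the baseline assessment and fixes when a volunteer enters the trial: "The volunteers will be considered participants in the study the moment the envelope is opened".
- **Control of bias** lists the safeguards of the design: "randomization process, allocation concealment, blinded assessment of the results and intention-to-treat analysis".
- **Treatment** gives both groups the same five balance games and gives Group II four strength games in addition.

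The planned size is small: "Forty patients with a diagnosis of HSP will be recruited", 20 per group. There are two assessments, one before rehabilitation and one after the 20th session. The list under Assessment of results contains no adverse-event or tolerability outcome, and no section provides for reporting how many participants were removed.

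**The concern.** Intention-to-treat means that everyone randomised is analysed in the group to which they were allocated. The Management rule instead takes randomised people out of the analysis, with the data already collected from them, because of an event that the study treatment can cause. An analyst cannot obey both sections. A separate analysis plan would not resolve this: following Management would breach Control of bias, and the reverse.

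Three things are at stake.

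- **Between-group comparison.** It can be biased if persisting discomfort is related to outcome and leads to different removals in the two arms. The four extra games in Group II make a difference possible.
- **Pre-post change.** Each outcome is judged by improvement from first to second assessment. Change in an arm can be inflated wherever discomfort is related to outcome, even if removals are balanced.
- **Tolerability.** The patients who tolerated the programme least drop out of the results, and the protocol has no other outcome that would show them.

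**Working it through.** **Does the rule reach randomised participants?**

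1. Randomization makes a volunteer a participant when the envelope is opened, and Management removes a participant.
2. The envelope is opened after the baseline assessment and before any session. Discomfort from rehabilitation, or from the second assessment, is therefore always after randomisation.
3. The remark that the patient is not put into another group presupposes an allocation.
4. Discomfort at the baseline assessment comes before the envelope. Excluding such a person breaches nothing, but the rule does not separate the two cases.

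So the conflict is real for everything after the envelope.

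**How large could the effect be?**

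The protocol gives no exclusion rate, effect size or SD, so there is no figure of its own to reproduce. What follows is an illustration.

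*From the protocol:* 20 per group, two assessments, repeated-measures ANOVA at 5%. With two time points, the group-by-time test is equivalent to a t-test on change, so the t-test is used here, two-sided (the protocol does not state sidedness).

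*Assumed:* no true difference; change standard normal; k of 20 removed from Group II and none from Group I; removal driven by a discomfort score with correlation ρ to poor change.

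*Formula:* expected bias = ρ × S(k) / (20 − k), where S(k) is the absolute sum of the expected k lowest of 20 standard normal values.

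*Check by hand, k = 3:* S(3) ≈ 4.41. At ρ = 1.0 the bias is 4.41 / 17 = 0.26 SD. At ρ = 0.5 it is 0.5 × 0.26 = 0.13 SD.

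*Simulation, 40,000 trials per cell (bias in SD of change; type I error):*

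| Removed from Group II | ρ = 0 | ρ = 0.3 | ρ = 0.5 | ρ = 1.0 |
|---|---|---|---|---|
| 2 of 20 | 0.00; 5.0% | 0.05; 5.3% | 0.09; 6.1% | 0.18; 9.9% |
| 3 of 20 | 0.00; 5.2% | 0.08; 5.6% | 0.13; 7.2% | 0.26; 14.4% |
| 4 of 20 | 0.00; 4.9% | 0.10; 6.2% | 0.17; 8.2% | 0.33; 19.4% |

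The k = 3 row agrees with the hand calculation.

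*Removals in both arms:* the biases subtract. One removal at ρ = 0.5 shifts an arm by 0.05 SD. With 1 removed from Group I and 2 from Group II, the net bias is 0.09 − 0.05 = 0.04 SD. With 2 from each, it is 0.09 − 0.09 = 0, although mean change within each arm is still raised by 0.09 SD.

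**Does keeping the collected data suffice?**

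No. Someone who stops during the 20 sessions has only a baseline assessment. A two-time-point ANOVA on complete cases drops that person anyway, so the bias in the table remains unless the second assessment is obtained or its absence is handled.

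**The case against.** The strongest case on the other side accepts the contradiction and disputes its reach.

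- **Worst responders.** A reader might infer that the rule removes the worst responders and so inflates every pre-post improvement. The protocol does not say so: the trigger is discomfort, not poor response, and the outcomes also include strength, cognition, pain and quality of life. The vestibular mechanism that Management names makes a link with the balance outcomes plausible, but it stays an inference. At ρ = 0 there is no bias.
- **Unequal arms.** Removals in Group II only are an assumption of the same weight as the number removed. The balance games are common to both arms. Treatment gives both groups 30 minutes, while Randomization allows 30 minutes to one hour, so a heavier total load in Group II is possible but not established.
- **Erased harms.** A reader might infer that records are destroyed and the only harm signal is erased. The text excludes data from the sample; it does not order destruction or forbid reporting removals. Dizziness impact and pain are measured by VADL and VAS. However, those values are excluded for the very patients concerned, and nothing requires the removals to be reported.
- **Consent.** Parts of Management address the participant directly, so patients may have been told that their data would be excluded. The consent form is not at hand.

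These points limit the size of the problem and what the remedy must cover. None of them reconciles Management with Control of bias.

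**Conclusion.** The point stands as an internal contradiction that must be resolved before analysis: for randomised participants, the data-exclusion rule and the intention-to-treat claim cannot both be followed.

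The size of the resulting bias is unknown. If 2 to 4 of 20 were removed from Group II only, with no true difference, it would be about 0.09-0.17 SD at correlation 0.5, with type I error about 6-8%. At correlation 1.0 it would be 0.18-0.33 SD, with type I error about 10-19%; that is a worst case. The between-group bias is nil if discomfort is unrelated to outcome, or if removals are balanced with equal correlation. The number removed, the one-sided pattern and the correlation are all assumptions.

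The contradiction itself and the missing account of removals depend on none of these figures.

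**What to change.** Reconcile Management with Control of bias by replacing the data-exclusion wording, for participants who stop after randomisation because of discomfort, with the following:

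1. They stay in their allocated group, and data already collected are retained unless they withdraw consent to their use.
2. The second assessment is sought at the planned time, about 10 weeks (20 sessions at two per week), where the participant agrees and the investigator considers it suitable.
3. The primary analysis includes all randomised participants, with a stated method for missing second assessments. Examples are a likelihood-based mixed model or multiple imputation, with a sensitivity analysis that assumes poorer outcomes in those who stopped.
4. The number stopping for discomfort is reported by arm.

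State separately that exclusion for discomfort at the baseline assessment, before the envelope is opened, is not a post-randomisation exclusion.

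If the consent form promised that data would be excluded, retention needs ethics committee approval or the participants' agreement. Failing that, withdraw the intention-to-treat claim for these participants and report the exclusions by arm.

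**Cost:** a short protocol amendment, second assessments for those who stopped, a missing-data method, and possibly ethics or consent action. No extra patients are needed. The Timeline says recruitment is complete, so for anyone already past the planned assessment time the missing-data method must carry the weight. The clinical decision to stop sessions is not affected.
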